#### Secondary outcome

Secondary objectives are local recurrence rate (LRR) and quality of life after the given treatment. All participating patients will have intensive follow-up during three years to evaluate the presence of locoregional and distal recurrent disease. Patients will be evaluated at the outpatient clinic every three months and MRI of the pelvis and CT scan of the thorax and abdomen are performed every six months. Patients who have been successfully treated with TEM will be followed with rectoscopy and ERUS every three months. Quality of life will be measured with the EORTC-QLQ-C30 and the EORTC-QLQ-C38 before CRT and four times during follow-up.

The following issues will also be registered and analysed for both the patients who undergo TEM and those undergoing TME: treatment related toxicity of the preoperative CRT and postoperative complications. The number of positive lymph nodes in TME patients will be assessed. This will give valuable information on the preoperative imaging modalities. All patients will be asked to consent with storage of tumour biopsies for translational research.

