### Interventions

#### Neoadjuvant chemoradiation therapy

All patients will receive neoadjuvant CRT, consisting of radiotherapy with a total dose of 50 Gy which is given in 25 fractions during 5 weeks. Patients will receive 825 mg/m^2 ^capecitabine b.i.d. 7 days per week during the whole treatment period. Six weeks after ending the CRT, therapy effect is evaluated by MRI, rectoscopy and ERUS. Patients with a clinical T0-2 tumour after CRT will undergo LE using TEM 8 - 10 weeks after the end of the neoadjuvant treatment. All other patients will undergo TME surgery.

After histological examination of the resected specimen, all patients with an ypT2-3 tumour, positive resection margins, or lymphangioinvasive growth, will undergo radical surgery within 4-6 weeks after the TEM-procedure.

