### Sample size calculation

Fifty-five patients will be included in this study. The study treatment protocol is considered successful if 30% or more of the included patients will complete CRT and undergo TEM surgery with complete resection of the ypT0-1 tumour. This means a resection with > 2 mm resection margin. A response of 15% or less will be considered a failure of this treatment modality. A three-step model for phase II cancer clinical trials will be used for calculating patient numbers with an alpha and beta of 0.1. An evaluation will be planned after 20 and 33 patients.

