After CRT, pCR has been reported in 8-27% of the patients [10-15]. This has led to evaluation of a wait and see strategy for patients with a clinical complete response (cCR), which is currently investigated for oncological safety by several investigators [42]. However, a pathological evaluation of the tumour remnant has several potential advantages to select patients for rectum sparing treatment. First of all, cCR is not always a pCR [42-45]. We have described a patient with a cCR, which demonstrated to be an ypT2 tumour after TEM, but eventually turned out to be a ypT3N1 tumour after TME surgery [45]. In these patients who seem to have a favourable response, a wait and see policy will delay adequate mesorectal excision. Secondly, a clinical partial response can be a pCR. In order to prevent patients with palpable tumour scarring from undergoing TME surgery, a biopsy of the scar seems to be the best option. Thirdly, patients with a near complete response after CRT (ypT1) can be adequately treated with a full thickness excision of the rectal wall.

The combination of TEM and CRT has been studied retrospective [46] and is studied in a similar protocol in the USA (ACOSOG Z0641 study) [47]. Local recurrence after a pCR (ypT0) has never been described, and also the local recurrence rate after a near complete response (ypT1) is reported to be low (0-6%). For ypT2 carcinomas, varying LRR have been described but are likely to be above 10% [46]. Despite these observations the ACOSOG Z0641 protocol prescribes a wait and see policy for ypT2 tumours [48]. We feel that this might not be an oncological save treatment and have therefore chosen to perform TME surgery in all patients with ypT2 and higher tumours and monitor long term outcome. Another interesting observation will be the registration of complications after TEM. In the case reports described in the literature, several patients experienced wound complications, but the exact rate will be established in this prospective analysis [49].

The trial accrual is expected to be adequate in the above mentioned centers and it is assumed that in two years all patients will be treated. This trial will give us an answer if this multimodality protocol for rectum saving treatment of rectal cancer is feasible and if so, a randomized phase III trial will be conducted.

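### CRT toxicity is to be analysed in groups defined by later surgery, so a patient who starts CRT but is never operated on belongs to neither group

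*Protocol article*

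**What the plan says.** **Secondary outcome (Outcome parameters).** Besides recurrence and quality of life, further items will be "registered and analysed for both the patients who undergo TEM and those undergoing TME: treatment related toxicity of the preoperative CRT and postoperative complications". No section names a toxicity population made up of all patients who started CRT.

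**Neoadjuvant chemoradiation therapy (Interventions).** CRT comes first and is universal: "All patients will receive neoadjuvant CRT, consisting of radiotherapy with a total dose of 50 Gy". The route is chosen after the response evaluation six weeks later: "Patients with a clinical T0-2 tumour after CRT will undergo LE using TEM 8 - 10 weeks after the end of the neoadjuvant treatment". For the rest, the text says: "All other patients will undergo TME surgery". After TEM, patients with an ypT2-3 tumour, involved margins or lymphangioinvasion "will undergo radical surgery within 4-6 weeks after the TEM-procedure". The Discussion calls this operation TME, saying that the authors "have therefore chosen to perform TME surgery in all patients with ypT2 and higher tumours".

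**Sample size calculation.** The strategy counts as a success if "30% or more of the included patients will complete CRT and undergo TEM surgery with complete resection of the ypT0-1 tumour". The denominator here is included patients. Completing CRT and having TEM are conditions that a patient may or may not meet.

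**The concern.** Toxicity of a preoperative treatment arises before surgery and can prevent it. Grouping patients by the operation they later had makes the analysis depend on a consequence of the exposure. The patients most likely to be missed are those with the worst outcome: death during or after CRT, or an event serious enough that no operation follows.

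This matters in this trial because long-course CRT is an added exposure for many of its patients. The Background gives short-course radiotherapy plus TME as the Dutch standard for T2-3 tumours without a threatened margin or N2 disease, and reserves long-course CRT for locally advanced disease. With 55 patients, a handful of losses moves a toxicity percentage noticeably.

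A second, smaller problem is that the two surgical groups overlap. A patient who has TEM and then completion surgery has undergone both operations. The text does not say whether that patient's toxicity and complications count under TEM, TME or both.

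**Working it through.** The plan attaches no figure to this item, so there is none to reproduce. The check has three parts.

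**1. Who is in the named groups.** Set the passages side by side:
- Interventions: all patients receive CRT; patients then go to TEM (clinical T0-2) or to TME (all others). No pathway without surgery is described.
- Secondary outcome: toxicity is analysed for those who undergo TEM and those who undergo TME.

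The two groups together equal everyone who started CRT only if nobody is lost between the start of CRT and surgery 8 to 10 weeks after its end. A patient lost in that interval is in neither group. A patient who stops CRT early but is later operated on remains in one of them.

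**2. Size of the effect, on assumed values.**

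Inputs:
- N = 55 (Sample size calculation), all taken to start CRT.
- k = number never operated on because of CRT toxicity, all counted as severe. Assumed: 1, 3, 5 or 8.
- s = number with severe toxicity among the N − k operated, taken as the whole number nearest to 10% or 30%. Assumed.

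Formulas:
- Operated only: q = s / (N − k)
- All who started CRT: (s + k) / N
- Understatement: (s + k)/N − s/(N − k) = (k/N) × (1 − q)

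| k | Operated only | All who started CRT | Understatement (points) |
|---|---|---|---|
| 1 | 5/54 = 9.3% to 16/54 = 29.6% | 6/55 = 10.9% to 17/55 = 30.9% | 1.6 to 1.3 |
| 3 | 5/52 = 9.6% to 16/52 = 30.8% | 8/55 = 14.5% to 19/55 = 34.5% | 4.9 to 3.8 |
| 5 | 5/50 = 10.0% to 15/50 = 30.0% | 10/55 = 18.2% to 20/55 = 36.4% | 8.2 to 6.4 |
| 8 | 5/47 = 10.6% to 14/47 = 29.8% | 13/55 = 23.6% to 22/55 = 40.0% | 13.0 to 10.2 |

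If only a share f of the unoperated had severe toxicity, the understatement becomes (k/N) × (f − q). It vanishes when f = q. The direction of the bias therefore rests on the unoperated having more severe toxicity than the operated, which is what one expects when toxicity is the reason for no surgery. Any CRT death before surgery is missed by an operated-only set whatever the other values.

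**3. Overlap.** Let T patients have TEM, D have TME first, and c have TEM and then TME. The patients who undergo TEM number T, and those undergoing TME number D + c. The groups sum to T + D + c, while the number operated on is T + D. The excess is c. The documents give no value for c.

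**The case against.** The strongest reply is that the sentence is meant inclusively: both groups, whichever operation. The Interventions section sends every patient to TEM or TME, so under the planned pathway the two groups are the whole cohort. The sentence may simply extend registration beyond the TEM patients. That is plausible, and it stands to this extent: there is no stated rule excluding unoperated patients. A reader might infer that the plan removes the worst toxicity by design, but the documents do not say so. The inclusive reading nevertheless fails for the patient who never reaches surgery. The same section refers to all patients outright for follow-up and for tissue storage, but names surgical groups for toxicity.

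The reply also says that an article may leave the safety set to the full protocol or analysis plan. That would hold if the article were silent. Here it names a population, and the population named does not fit the outcome.

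Three further inferences are not supported:
- **That the success criterion proves an unoperated group exists.** A patient who does not meet it may simply have had TME first. It shows only that the primary denominator allows for attrition while the toxicity wording does not.
- **That the burden of two operations would be invisible.** Complications are to be registered for both procedures, and the patients who have both can be identified. What is missing is a rule for where they count.
- **That this toxicity analysis decides whether phase III goes ahead.** The Discussion makes phase III conditional on feasibility, and success is defined on complete resection of an ypT0-1 tumour.

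**Conclusion.** The point holds as a badly fixed population for a descriptive secondary safety item. As written, CRT toxicity is tied to groups formed after CRT, and a patient who starts CRT but has no operation is in neither. On assumed values (1 to 8 of 55 lost before surgery through toxicity, all counted as severe; about 10 to 30% severe toxicity among the operated), severe toxicity is understated by about 1 to 13 percentage points. If every patient reaches surgery, there is no loss at all.

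The overlap of TEM-then-TME patients is real but is mainly a reporting ambiguity. No comparison of TEM with TME is described that it would bias.

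The primary endpoint is counted over included patients and is not affected.

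**What to change.** In the Secondary outcome section, state that CRT toxicity, including deaths, is analysed in all patients who start CRT, regardless of later surgery. State that postoperative complications are reported per procedure, with three mutually exclusive groups shown separately: TEM only, TEM followed by TME, and TME first.

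The cost is one or two sentences and one extra table layout. No additional patients are needed and the design does not change. The one practical condition is that toxicity forms are completed for patients who leave before surgery.

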### Sample size calculation

Fifty-five patients will be included in this study. The study treatment protocol is considered successful if 30% or more of the included patients will complete CRT and undergo TEM surgery with complete resection of the ypT0-1 tumour. This means a resection with > 2 mm resection margin. A response of 15% or less will be considered a failure of this treatment modality. A three-step model for phase II cancer clinical trials will be used for calculating patient numbers with an alpha and beta of 0.1. An evaluation will be planned after 20 and 33 patients.

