### Outcome parameters

#### Primary outcome

Primary objective of the study is to demonstrate that more than 12 of 55 patients have minimal residual disease 8 - 10 weeks after neoadjuvant CRT. Minimal residual disease is defined as an ypT0 or ypT1 stage.

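### The sample size section words the design rates of 15% and 30% as verdicts on the observed rate, which conflicts with the 13-of-55 threshold in the primary outcome

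*Protocol article*

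**What the plan says.** Three places in the Protocol article bear on what counts as success.

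- **Sample size calculation.** "Fifty-five patients will be included in this study". On success, the section says: "The study treatment protocol is considered successful if 30% or more of the included patients will complete CRT and undergo TEM surgery". The tumour must also be ypT0-1 and fully removed, explained as a margin above 2 mm. On failure, it says: "A response of 15% or less will be considered a failure of this treatment modality". A three-step phase II model is then named for "calculating patient numbers with an alpha and beta of 0.1", and "An evaluation will be planned after 20 and 33 patients". No stopping boundaries are given.
- **Primary outcome.** The stated aim is to "demonstrate that more than 12 of 55 patients have minimal residual disease" at 8 to 10 weeks after chemoradiation. "Minimal residual disease is defined as an ypT0 or ypT1 stage".
- **Objectives.** The primary objective is again ypT0-1 after chemoradiation and TEM, here with a complete specimen (margin above 2 mm) and no nodal metastases in it.

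No sentence calls 30% or 15% a true, assumed, null or alternative rate, and none connects the count of 12 to either percentage.

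**The concern.** In a single-arm phase II design, p0 and p1 are true response rates at which the error probabilities are fixed. The observed rate needed for success lies between them. The sample size section instead attaches a verdict to each rate, success at one and failure at the other, among the patients included in this trial. Read as written, these are cut-offs for the observed proportion, and they do not agree with the count under Primary outcome.

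The Discussion says that a randomised phase III trial will follow if the treatment proves feasible. The threshold therefore drives a go/no-go decision. With two thresholds in print, a result between them can be reported either way, and the choice could be made after the result is known.

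**Working it through.** **Inputs.** From Sample size calculation: n = 55, looks at 20 and 33, rates of 15% and 30%, alpha = beta = 0.1. From Primary outcome: more than 12 of 55. Assumed: a one-sided test, and futility-only stopping. Where interim stops are used, they are at 2 or fewer of 20 and 5 or fewer of 33. The article gives neither boundary.

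**Step 1: reproduce N = 55.** Take p0 = 0.15 and p1 = 0.30 as true rates. The smallest exact single-stage design has n = 53 with success at 12 or more (alpha 0.0907, power 0.9094). With looks at 20, 33 and 55, final cut-offs of 12, 13, 14 and 17 or more were searched with futility-only boundaries. One set met both limits: stop at 2 or fewer of 20 and at 5 or fewer of 33, success at 12 or more of 55 (alpha 0.0985, power 0.9006). So 55 is reproduced when 30% is the design alternative, and not when it is the observed cut-off.

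**Step 2: turn the wording into counts.**
- Success at 30% or more: 0.30 × 55 = 16.5, so at least 17 (17/55 = 30.9%).
- Failure at 15% or less: 0.15 × 55 = 8.25, so at most 8.
- More than 12: at least 13 (13/55 = 23.6%).

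Counts of 13 to 16 (23.6% to 29.1%) meet the primary outcome statement but not the success statement in the sample size section. That section gives no verdict for 9 to 16.

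**Step 3: operating characteristics.** Type I error is P(X ≥ r | n = 55, p = 0.15) and power is P(X ≥ r | n = 55, p = 0.30), exact binomial.

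| Final rule | Alpha, no stops | Power, no stops | Alpha, assumed stops | Power, assumed stops |
|---|---|---|---|---|
| at least 12 | 0.1129 | 0.9332 | 0.0985 | 0.9006 |
| at least 13 | 0.0603 | 0.8823 | 0.0555 | 0.8589 |
| at least 17 | 0.0022 | 0.4921 | 0.0022 | 0.4895 |

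**Step 4: how often the count falls in the gap** (no interim stops).
- P(13 to 16) at a true 30% = P(X ≥ 13) − P(X ≥ 17) = 0.8823 − 0.4921 = 0.3902.
- The same probability is 0.058 at a true 15%, 0.261 at 20% and 0.449 at 25%.
- P(9 to 16) at a true 30% = 0.5013.

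Step 4 treats the two sections as counting the same event. They do not quite: the sample size section requires completed chemoradiation, TEM and a margin above 2 mm, whereas the primary outcome requires only ypT0-1. Under the narrower definition the count can only be equal or lower.

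**The case against.** The strongest defence is that the two percentages stand under a sample size heading, directly before the named phase II model, and are the only rates given for it. A statistician would take them as p0 and p1. On that reading one section gives design rates, the other gives the resulting count, and a final boundary of about 12 or 13 of 55 is what those rates produce. This is very probably what was meant, and step 1 supports it. It does not remove the defect: the sentence still gives a verdict in terms of the included patients, and nothing in the article says otherwise.

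Three stronger readings are tempting, and the article does not support them.

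- *That 13 to 16 successes both pass and fail.* The sample size section reserves failure for 15% or less, so these counts are unclassified there.
- *That the trial has only 49% power.* Nothing suggests that it was sized with a cut-off of 17. The figure describes the literal rule only.
- *That the correct cut-off must be at least 12.* This rests on assumed futility boundaries. The condensed article may leave the real ones to the full protocol, and their absence here is no fault.

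**Conclusion.** The concern holds as a conflict between two printed decision thresholds, caused by wording the design rates as verdicts on the observed rate. The sample size itself is sound. The 13-to-16 gap follows from the text alone. Its 39% probability assumes a true rate of 30%, n = 55 without interim stops, and a common event.

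If the 30% rule were applied literally, power at a true 30% would be 49.2% against a planned 90%, and type I error 0.2% against 10%. Neither figure needs any interim boundary, and the assumed futility stops barely move them (power 49.0%).

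A smaller point follows: the explicit count does not quite meet the stated beta. Requiring at least 13 gives at most 88.2% power, since futility stops can only lower it. That would fit an off-by-one slip from at least 12, but the article cannot settle this.

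**What to change.** 1. In Sample size calculation, state 15% and 30% as the true rates p0 and p1, and delete them as success and failure verdicts on the observed rate.
2. State one final-stage count, taken from the actual three-stage design, in the same words there and under Primary outcome.
3. Apply that count to one event definition, used identically in Objectives, Primary outcome and Sample size calculation. It should say whether completed chemoradiation, TEM, the margin above 2 mm and the nodal condition are part of the event.
4. Check the count against alpha = beta = 0.1 with the real interim boundaries. If more than 12 is kept, restate the power: 88.2% without stops, 85.9% under the stops assumed here. If the design's boundary proves to be at least 12, correct the primary outcome.

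This is a change of wording with no extra patients. If the operative count moves from 13 to 12, that is a change of decision rule and should be documented before outcomes are known.

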### Objectives

Primary objective of the study is to determine the number of patients with minimal residual disease (ypT0-1) after neoadjuvant CRT followed by TEM surgery. The resection specimen should be complete (> 2 mm margin) without evidence of nodal metastases (if nodes are found in the full thickness specimen). Secondary objectives are quality of life and local recurrence rate.

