### Design

This study is a non-randomized feasibility study to determine whether radiotherapy combined with capecitabine followed by organ-sparing surgery using TEM can be considered as a valid new treatment modality in distal rectal cancer. The flow chart of the study is showed in Figure 1.

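### A completely excised ypT1 tumour with lymphangioinvasive growth counts as a primary success, although the protocol sends that patient to radical surgery

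*Protocol article*

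**What the plan says.** The protocol article describes primary success in three places.

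- **Primary outcome:** "Minimal residual disease is defined as an ypT0 or ypT1 stage". Nothing is said here about margin, nodes or lymphangioinvasion.
- **Sample size calculation:** the treatment protocol succeeds if at least 30% of included patients complete chemoradiation and "undergo TEM surgery with complete resection of the ypT0-1 tumour. This means a resection with > 2 mm resection margin".
- **Objectives:** "The resection specimen should be complete (> 2 mm margin) without evidence of nodal metastases (if nodes are found in the full thickness specimen". This adds a nodal condition, limited to nodes that happen to lie in the TEM specimen.

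The rule for surgery after TEM is under Interventions, Neoadjuvant chemoradiation therapy: "all patients with an ypT2-3 tumour, positive resection margins, or lymphangioinvasive growth, will undergo radical surgery within 4-6 weeks after the TEM-procedure". The three triggers are joined by an *or*, so each is enough alone.

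The Design section gives the purpose: to find out whether chemoradiation "followed by organ-sparing surgery using TEM can be considered as a valid new treatment modality in distal rectal cancer". The Hypothesis section likewise speaks of rectum-saving treatment.

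**The concern.** Consider a patient who completes chemoradiation, has TEM, and is found to have a ypT1 tumour removed with more than 2 mm margin, no involved nodes in the specimen, and lymphangioinvasive growth. This patient meets all three descriptions of success. The same histology report sends the patient to radical surgery. For a strategy meant to avoid such surgery, that is not a success.

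The primary count decides whether the approach is judged feasible, and the Discussion makes a phase III trial depend on that answer. One patient is 1/55 = 1.8 percentage points, so one or two such patients can carry the result across the boundary. If the scoring is left open until results are known, classifying them becomes a data-driven choice.

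**Working it through.** **1. Success definitions against the surgery rule**

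| Trigger for radical surgery after TEM | Excluded by Primary outcome? | By Objectives? | By Sample size calculation? |
|---|---|---|---|
| ypT2-3 | yes | yes | yes |
| Positive margin | no | yes (> 2 mm) | yes (> 2 mm) |
| Lymphangioinvasive growth | no | no | no |

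Only the third trigger is excluded nowhere. Since ypT0 leaves no residual primary tumour, the overlap can arise essentially only in ypT1.

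**2. The plan's own sample size**

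Inputs from the article: p0 = 0.15, p1 = 0.30, alpha = beta = 0.1, looks after 20 and 33 patients, 55 in total. The interim bounds are not printed and are inferred here; one-sided testing is assumed.

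Let X1 ~ Bin(20, p), X2 ~ Bin(13, p), X3 ~ Bin(22, p). With stopping at ≤2/20 or ≤5/33 and final cut-off c:

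P(success | p) = P(X1 ≥ 3, X1 + X2 ≥ 6, X1 + X2 + X3 ≥ c)

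- c = 12: alpha 0.0985, power 0.9006. This meets the stated error rates, so N = 55 is reproduced.
- c = 13, which is the printed rule of more than 12 of 55: at p = 0.15 the probability is 0.056, and power at 0.30 is 0.859.

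**3. Effect of the overlap on a false positive conclusion**

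Let r = 0.15 be the rate of successes *not* sent to radical surgery, and f the share of counted successes that are lymphangioinvasive. The counted rate is q = r/(1 − f). The article gives no f, so every non-zero row is an assumption.

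| Assumption | Counted rate q | P(success), ≥13 (printed) | P(success), ≥12 |
|---|---|---|---|
| none (f = 0) | 0.150 | 5.6% | 9.9% |
| f = 5% | 0.15/0.95 = 0.158 | 7.7% | 13.1% |
| f = 10% | 0.15/0.90 = 0.167 | 10.8% | 17.3% |
| a further 2% of all patients (f = 2/17 = 12%) | 0.17 | 12.1% | 19.0% |
| a further 4% of all patients (f = 4/19 = 21%) | 0.19 | 21.9% | 31.1% |

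The inferred interim bounds matter little. With no interim stopping and ≥13, the first three rows become 6.0%, 8.4% and 11.6%.

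**4. Effect of the stricter definition on power**

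If the 30% target was set for the looser count, the stricter rate is 0.30 × (1 − f).

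| f | Rate | Power, ≥13 | Power, ≥12 |
|---|---|---|---|
| 0 | 0.300 | 0.859 | 0.901 |
| 2% | 0.294 | 0.838 | 0.885 |
| 5% | 0.285 | 0.802 | 0.858 |
| 10% | 0.270 | 0.730 | 0.802 |

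**The case against.** The strongest reply is that the endpoint is pathological response. The Abstract, Objectives and Primary outcome define it by ypT stage, the Hypothesis is motivated by published complete-response rates, and the sample size section itself calls the quantity a response. On that reading a ypT1 tumour with lymphangioinvasion is classified correctly, and declaring success at a true response of 17% or 19% is not a type I error, since those rates lie between the design's 15% and 30%.

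This is fair about the wording but does not settle the matter. The sample size section uses the count to judge the treatment protocol and calls a low rate a failure of the modality. It also requires completed chemoradiation, TEM and a clear margin, none of which a pure response endpoint needs. Having excluded two of the three surgery triggers, it gives no reason for admitting the third. What stands is that the table in step 3 gives false-success probabilities only if the 15% threshold is applied to successes not sent to radical surgery.

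Three further replies stand:

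- The frequency of lymphangioinvasion is not in the document and could be zero.
- Affected patients would not go unseen. The Secondary outcome section registers complications for both TEM and TME patients and assesses positive nodes after TME. This does not correct the primary count.
- The article is condensed and its flow chart is not shown. The full protocol may say how these patients are scored, so confidence attaches to the mismatch in this text and not to its numerical effect.

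**Conclusion.** The mismatch is real and nothing in the article resolves it: the primary count can include patients whom the protocol sends to radical surgery. The effect on the success rate is upward or nil, never downward. Under the printed rule and the inferred interim bounds, the chance of declaring success at a 15% rate of successes not sent to radical surgery goes from 5.6% to between 7.7% and 10.8% for an assumed 5% to 10% share. At the lower end of that range it stays below the planned 0.1.

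A reader might go further in three ways that the documents do not support.

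- *The false-success risk is 19% or 31%.* These figures need a cut-off of ≥12, which is not the printed rule, and 12% or 21% of counted successes being lymphangioinvasive, for which the article gives no source. With the printed rule the same assumptions give 12.1% and 21.9%.
- *These patients lose the rectum.* The article says radical surgery and gives no figure for its outcome.
- *The sample size is wrong.* N = 55 is reproduced; the problem lies in the definition.

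The endpoint should be corrected before results are seen, but the point does not undermine the design.

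**What to change.** Reconcile the Objectives, Primary outcome and Sample size sections with the rule for surgery after TEM, leaving that rule unchanged. Use one definition in all three places, for example: *primary success is completed chemoradiation and TEM with complete resection (> 2 mm margin) of a ypT0-1 tumour, no nodal metastases in the specimen, and no finding on TEM histology that the protocol makes a trigger for radical surgery, including lymphangioinvasive growth.* Report ypT0-1 irrespective of lymphangioinvasion as a secondary pathological response rate, so that comparison with published response rates remains possible.

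The cost is one clause. The histology is already examined for the surgery decision, and N stays at 55. The headline rate may be slightly lower. If the 30% target was meant for the looser count, power under the printed rule falls from 0.859 to 0.838 for a 2% share and to 0.802 for a 5% share. It would reach 0.730 only if a full 10% of counted successes were affected.
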